#### Child and parent characteristics

A computer-assisted telephone interview with parents will be conducted to collect: child and parent demographic information (age, gender, household income, and parent education); usual parent physical activity; and child and parent height and weight, using items from the New South Wales Population Health Survey [33] and items to assess the home environment from the preschool age physical activity questionnaire (Pre-PAQ) questionnaire [34]. The survey will be conducted at baseline and follow-up.

#### Service characteristics

During a telephone interview with supervisors of participating childcare services the following service characteristics will be assessed: postcode of locality (to assess the socioeconomic status of the area) [35]; number of years in operation; total number of 3 to 6 year-old children enrolled; number of staff; staff qualifications; and service governance (Department of Education service or privately owned). Such items were drawn from previous studies [17, 24].

#### Service outdoor free-play schedule and physical activity environment

Observations at childcare services will be conducted by data collectors (not blind to group allocation) to record the duration (via stop watch), timing and frequency of outdoor free-play to ensure that services are implementing outdoor free-play periods consistent with the study protocol. Data collectors will also collect information regarding the childcare service physical activity environment using a comprehensive environment assessment tool (Environment and Policy Assessment and Observation instrument, EPAO) [36]. The following types of physical activity observation elements will be conducted: Active play opportunities, sedentary opportunities, sedentary environment, portable play environment, fixed play environment, staff behaviour physical activity, physical activity training and education and physical activity policy.

### Intervention fidelity

The research team will visit the services during the intervention period to observe if childcare services have implemented the intervention prior to follow-up data collection. A checklist developed by the research team will be used to monitor whether the intervention was delivered as per the study protocol on the day of data collection.

### Analysis

Minutes of MVPA will be determined using age-specific child-validated equations (cut points) [29]. Generalised Linear Mixed Models (GLMM), to take account of the repeated measures on children (daily measures during baseline and follow-up periods) as well as clustering of individuals within services, will be used under an intention to treat framework to test for a difference in change in minutes of MVPA between groups. The GLMM will include terms for time (baseline and follow-up), group (intervention or control group), and the interaction of time and group, and will control for child gender and total outdoor play time. A sensitivity analysis will be performed using multiple imputation for missing data to assess robustness of the main analysis [37]. Per protocol analysis will be performed using services that implemented the intervention as intended and subgroup analysis undertaken by gender and baseline physical activity levels of children.

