**Methods:**

The study will employ a between group cluster randomised controlled trial design. Fourteen childcare services in the Hunter New England region of New South Wales, Australia, who currently implement a single session of free outdoor play between their core operational hours of 9 am to 3 pm will be recruited into the trial. Childcare services will be randomised to an intervention or a no intervention control group. Childcare services in the intervention group will be supported by an early childhood education specialist to provide three periods of outdoor free play for children between the hours of 9 am to 3 pm. Each period of outdoor free play will be at least 15 min in duration but must equate to their total usual duration of outdoor play. Services in the control group will continue to implement a single period of outdoor play. The primary trial outcome is minutes of time children spend in MVPA whilst in care assessed objectively via accelerometer over 5 days. Outcome assessment will occur at baseline and 3 months post baseline. Generalised Linear Mixed Models (GLMM) under an intention to treat framework will be used to compare differences between groups in the primary trial outcome at follow-up. Sensitivity analysis will be conducted to test assumptions of missing data. Per protocol analysis will be performed using services that implemented the intervention as intended and subgroup analysis undertaken by gender and baseline physical activity levels of children.

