## Methods

### Design

The study will employ a between group, cluster randomised controlled trial design (see Fig. 1). Fourteen centre-based childcare services with one period of outdoor free-play (of at least 45 min duration) will be randomised to an intervention or control group. Intervention services will change their scheduling of outdoor free-play such that their usual total time for outdoor free-play is broken into multiple separate periods of at least 15 min in duration each with an indoor period of at least 30 min in between. Control services will continue to provide their usual total period of outdoor free-play time across a single continuous period. Intervention efficacy will be determined by comparing differences between groups in the minutes children spend in MVPA per day at childcare. MVPA will be assessed via accelerometer over 5 days at baseline and 3 months later. Approval to conduct the study was obtained from Hunter New England Human Research Ethics Committee (reference number 15/11/18/4.03) and the University of Newcastle Human Research Ethics Committee (reference number H-2016-0088).

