### Intervention

The intervention will seek to create a childcare environment more supportive of child physical activity by scheduling multiple opportunities for outdoor free-play in a way which is consistent with children’s developing fitness levels [25] and natural physical activity patterns [10, 13, 26]. Specifically, within a 6 h day (9 am to 3 pm) the intervention will divide their usual total time of outdoor free-play for children across three periods of at least 15 min duration.

Three periods of outdoor free-play was selected as: i) research has demonstrated repeated spikes in activity across the day in childcare coinciding with scheduled breaks [13, 16]; and ii) that the start of such breaks stimulate between 3 and 15 min of intense activity, sufficient to achieve an additional 10 min MVPA [27]. The minimum period of outdoor free-play of 15 min was selected given evidence that MVPA often attenuates after this period [13]. Furthermore, services will be required to schedule at least 30 min of indoor time (structured or unstructured play) between periods of outdoor free-play, based on evidence that children may be more likely to be moderate-to-vigorously physically active following prolonged indoor periods [28]. Immediately following baseline data collection, intervention services will be supported by a member of the research team and an early childhood education specialist to implement the intervention. This support will include written materials and at least two site visits and two telephone support calls prior to follow-up data collection to re-orient their operations to incorporate the scheduling change. No other intervention support will be provided to children, childcare service staff or parents.

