### Sample size and power calculation

The study will approach approximately 500 children from 14 childcare services across the study region. Assuming the standard deviation of MVPA is 2.7 min/h [38] and assuming an intraclass correlation coefficient of 0.1 [39], a sample of 14 children per cluster (assuming a conservative participation rate of approximately 50 and a 20 % loss to follow-up) will provide the study with 80 % power to detect a change of 9.9 min in MVPA. An increase of 10 min of MVPA in children aged 3 to 6 years old has been found to have clinically significant beneficial effects on fat mass and peak bone mass [3, 4].

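### The primary contrast is stated in two ways, and the difference-in-change test uses the baseline data less efficiently than a baseline-adjusted comparison unless the baseline to follow-up correlation is high

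*Protocol article*

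**What the plan says.** The article describes the primary comparison in four places.

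- **Abstract, Methods:** the mixed model "will be used to compare differences between groups in the primary trial outcome at follow-up".
- **Design:** efficacy is judged by "comparing differences between groups in the minutes children spend in MVPA per day at childcare". This names neither change nor follow-up.
- **Analysis:** the model is used "to test for a difference in change in minutes of MVPA between groups". Its terms are explicit: "The GLMM will include terms for time (baseline and follow-up), group (intervention or control group), and the interaction of time and group". It also controls for gender and total outdoor play time. Baseline and follow-up daily measures are both outcomes. Baseline MVPA is not a covariate, and the arms' baseline means are not constrained to be equal.
- **Sample size and power calculation:** 80 % "power to detect a change of 9.9 min in MVPA", from a standard deviation, an intraclass correlation and a cluster size. No significance level and no baseline to follow-up correlation are given.

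**The concern.** Two different contrasts are described for one primary outcome. With seven services per arm, a chance baseline imbalance in MVPA is likely. A comparison at follow-up and a comparison of change would then give different estimates and p-values, and a confirmatory trial should say in advance which one counts.

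The second issue is precision. With a free group main effect, the time by group term is a difference in differences: it subtracts the whole of the observed baseline difference between arms. Randomisation makes that difference zero in expectation, so full subtraction over-corrects whenever r is below 1. Adjusting for baseline subtracts only the part that predicts follow-up.

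Third, the power statement speaks of a change, but the planned change test has the stated detectable difference only at one particular value of r.

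**Working it through.** **Inputs from the article.** "Assuming the standard deviation of MVPA is 2.7 min/h", which over the 9 am to 3 pm day is 2.7 × 6 = 16.2 min; "assuming an intraclass correlation coefficient of 0.1"; 14 children analysed per service; 14 services allocated 1:1, so 7 per arm and 7 × 14 = 98 children per arm.

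**Assumptions.** A two-sided 5 % level (none is stated) and a range for r.

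**Step 1: reproduce the plan's figure.**
- Design effect = 1 + (14 − 1) × 0.1 = 2.3.
- Effective sample size per arm = 98 / 2.3 = 42.6.
- SE = 16.2 × √(2 / 42.6) = 3.51 min.
- Detectable difference at 80 % power = (1.96 + 0.842) × 3.51 = 9.83 min, or 9.88 to 9.95 min with t quantiles on 194 or 83 df. Power at 9.9 min is 80.5 %.

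The stated 9.9 min is therefore reproduced as a comparison at one time point. No term for r enters.

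**Step 2: variance of each contrast.** Let V = 3.51².
- Follow-up only: V.
- Change: 2(1 − r)V.
- Baseline-adjusted, large sample: (1 − r²)V.

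The ratio of change to adjusted is 2(1 − r) / (1 − r²) = 2 / (1 + r): 1.54 at r = 0.3, 1.33 at 0.5, 1.18 at 0.7. The change variance equals V only at r = 0.5 and exceeds it below that. Under the normal approximation of Step 1, the change test detects 11.63 min at r = 0.3 (66 % power at 9.9 min), 9.83 min at r = 0.5 and 7.62 min at r = 0.7 (95 %).

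**Step 3: charge the small-sample cost.** There are 14 services, so a service-level analysis has 12 df for change. Adjusting on service means leaves 11 df, and estimating the slope inflates the variance by about 10 % (1 + 1/(12 − 2) = 1.10). Noncentral t calculations then give:

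| r | SE, change | SE, adjusted × √1.10 | Power at 9.9 min, change (12 df) | Power at 9.9 min, adjusted (11 df) | Detectable, change | Detectable, adjusted |
|---|---|---|---|---|---|---|
| 0.3 | 4.15 | 3.51 | 59 % | 73 % | 12.7 min | 10.8 min |
| 0.5 | 3.51 | 3.19 | 74 % | 81 % | 10.7 min | 9.8 min |
| 0.7 | 2.72 | 2.63 | 92 % | 93 % | 8.3 min | 8.1 min |
| 0.8 | 2.22 | 2.21 | 98 % | 98 % | 6.78 min | 6.80 min |
| 0.9 | 1.57 | 1.61 | about 100 % | about 100 % | 4.79 min | 4.94 min |

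Follow-up only on 12 df has 74 % power and detects 10.7 min at every r. At r = 0.3 the adjusted analysis therefore does no better than follow-up alone, but it is still well ahead of change.

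**Step 4: simulation.** Analyses of 14 simulated service means (4,000 runs per setting) gave power for change and adjusted of 64 % and 76 % at r = 0.38, 71 % and 79 % at 0.46, 86 % and 89 % at 0.64, 93 % and 94 % at 0.72, and 99 % for both at 0.82. Type I error was near 5 % for both methods.

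**The case against.** The planned model is standard and valid. Under randomisation the change and follow-up contrasts target the same effect, both are unbiased, and both hold their type I error. A reader might infer a biased primary analysis; nothing in the article supports that. The Analysis section lists the model terms explicitly and the abstract is a summary, so the room for choosing a contrast afterwards is narrower than it first looks. It remains current text against current text, and one of the two should change.

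A reader might also infer that the baseline data are wasted. They are not: the model uses them jointly with follow-up, and above r = 0.5 the change contrast is more precise than follow-up alone (8.3 against 10.7 min at r = 0.7).

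Nor is adjustment free. The slope and the lost degree of freedom cancel the gain by about r = 0.8. The same children are measured about 3 months apart, over up to 5 days each time, so a high r cannot be excluded. A child-level or constrained model may cost less, but that was not computed.

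Finally, the 9.9 min figure is conservative for the change test when r exceeds 0.5 (normal approximation), so the documents do not show that the trial is underpowered. All of this stands. It limits the size of the point but does not remove it.

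**Conclusion.** The point holds as one of pre-specification and efficiency. The primary contrast is described in two ways and should be described in one. The contrast in the Analysis section is inefficient by an amount that depends on r. Under the plan's inputs, a two-sided 5 % level and adjustment on service means, baseline adjustment adds about 14 percentage points of power at r = 0.3, 7 at r = 0.5 and 1 at r = 0.7, and nothing from about r = 0.8. The power text corresponds to the planned test only at r = 0.5, and that only under the normal approximation.

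Since r is not in the article, no single figure for the loss can be defended. The inconsistency between the abstract and the Analysis section does not depend on r.

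**What to change.** Name one primary contrast and use the same words in the abstract, Design, Analysis, and Sample size and power calculation. The preferred choice is the between-group difference in MVPA at follow-up, adjusted for baseline MVPA.

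An alternative is the same longitudinal model with a common baseline mean (no group difference at baseline). This also keeps children who have only one of the two measurements. It needs baselines that are equal in expectation, so it suits the trial only if children were recruited before services were randomised, or without knowledge of allocation. The article does not state that order.

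In either case, use small-sample degrees of freedom for 14 services, and state the assumed r in the power text with a range around it.

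**Cost:** no new data are needed. Adjustment takes up to one degree of freedom and a small amount of variance for the estimated slope (about 10 % if done purely on service means), with a trivial loss of precision if r is about 0.8 or higher. The covariate version also needs a rule for children without baseline data.

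### The only missing-data sensitivity analysis named is multiple imputation, which unless specified otherwise shares the primary model's missing-at-random assumption and so does not probe departures from it

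*Protocol article*

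**What the plan says.** The Methods part of the Abstract gives the purpose: "Sensitivity analysis will be conducted to test assumptions of missing data". The Analysis section gives the method: "A sensitivity analysis will be performed using multiple imputation for missing data to assess robustness of the main analysis". No other missing-data analysis is named, and neither place says which assumption is meant.

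The main analysis is described as "Generalised Linear Mixed Models (GLMM), to take account of the repeated measures on children (daily measures during baseline and follow-up periods"), with clustering of children within services. On its structure the section says: "The GLMM will include terms for time (baseline and follow-up), group (intervention or control group), and the interaction of time and group". It also adjusts for gender and total outdoor play time.

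The sample size section plans for missing follow-up, "assuming a conservative participation rate of approximately 50 and a 20 % loss to follow-up".

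**The concern.** A sensitivity analysis for missing data is informative about an assumption only if it relaxes that assumption. A mixed model fitted by likelihood to every available day gives valid estimates if, given the observed data in the model, being missing does not depend on the unseen values. Multiple imputation as usually run draws the missing values under that same condition. If children lost to follow-up differ from otherwise similar children who stay, both analyses err in the same direction and by about the same amount.

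The risk is one of interpretation. Two nearly equal estimates would be reported as evidence that the result is robust to the planned loss, when near-equality was to be expected whether or not the assumption holds. The stated purpose and the only stated method do not match.

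**Working it through.** **1. The plan's own figure, to fix the scale.** Inputs from the sample size section: "Assuming the standard deviation of MVPA is 2.7 min/h", "assuming an intraclass correlation coefficient of 0.1", "a sample of 14 children per cluster", 14 services, 80 % power for 9.9 min. The 6 h day comes from the Intervention section and the 1:1 allocation from the randomisation section. Two-sided alpha of 0.05 is assumed, as the article does not state it.

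- SD per day = 2.7 x 6 = 16.2 min.
- Design effect = 1 + (14 - 1) x 0.1 = 2.3.
- Effective n per arm = 7 x 14 / 2.3 = 42.6.
- Power at 9.9 min (normal approximation) = 80.5 %, which reproduces the stated 80 %.
- Children per service after loss = 500 x 0.5 x 0.8 / 14 = 14.3, which agrees with 14.
- Standard error of the difference = 16.2 x sqrt(2 / 42.6) = 3.5 min. The smallest significant estimate is therefore about 1.96 x 3.51 = 6.9 min.

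**2. Do the two analyses move together?** Two-wave clustered data were simulated with SD 16.2 min, intraclass correlation 0.1, a true effect of 10 min and 200 replicates. The missingness model and the correlation between waves (0.6) are assumptions. There were 60 services per arm with 18 children each, so that bias stands clear of noise. The likelihood estimate was the two-wave normal version. Imputation was done by arm from baseline MVPA only, with no auxiliary variables and no service term, and only point estimates were compared.

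| Loss mechanism | Missing follow-up | Likelihood | Standard imputation | Imputation, intervention arm shifted by -10 min |
|---|---|---|---|---|
| At random | 19 % | 9.96 | 9.95 | 7.83 |
| Not at random (less active intervention children lost more often) | 17 % | 11.81 | 11.81 | 9.93 |

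Under both mechanisms the two standard analyses agree to within 0.01 min, and their estimates correlate at 0.99 across replicates. Under not-at-random loss both are about 1.8 min too high, and comparing them gives no sign of it. Only the shifted imputation shows how far the answer depends on the assumption.

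**3. Size in this trial.** If a fraction p of an arm is missing and those children differ by delta from their missing-at-random prediction, that arm's mean moves by p x delta. The effect moves by p1 x delta1 - p0 x delta0 (1 = intervention, 0 = control). With p = 0.2 and a departure in one arm only:

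- delta = 5 min: 0.2 x 5 = 1 min
- delta = 10 min: 0.2 x 10 = 2 min
- delta = 15 min: 0.2 x 15 = 3 min

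The range 5 to 15 min is assumed; 15 min is 15 / 16.2 = 0.93 of an SD. With equal loss and equal departure in both arms, 0.2 x delta - 0.2 x delta = 0.

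**4. Against the significance threshold.** With the standard error held at 3.5 min, a 2 min downward shift removes significance from an estimate between 6.9 and 8.9 min. An estimate of exactly 9.9 min would tip at a one-arm departure of (9.9 - 6.9) / 0.2 = 15 min.

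**The case against.** The strongest reply is that the article does not commit to plain missing-at-random imputation. It gives no imputation model, imputation can also be run under not-at-random assumptions, and such detail normally sits in an analysis plan that is not shown. That stands as far as detail goes: leaving out the imputation model or its variables is not a fault here. What remains is a stated purpose paired with one stated method which, as worded, does not serve it.

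Second, the Analysis section itself speaks only of robustness; the stronger wording is in the Abstract, which names no assumption. This is correct, and it is why part of the remedy is a change of wording.

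Third, imputation can draw on data outside the mixed model: the parent interview (income, education, parent activity, child height and weight, home environment) and out-of-care accelerometry where consented. The two analyses could then differ, and the comparison would say something about the choice of conditioning variables. This also stands. A reader might infer that the planned imputation is worthless and should be dropped; the documents do not support that. It would still, however, assume missing at random given a larger set of variables.

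A reader might also infer that the imputation will ignore services and so understate the standard error. Nothing says so, and the Analysis section explicitly recognises clustering.

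**Conclusion.** The point holds as a mismatch between purpose and method. Unless specified otherwise, the planned imputation and the primary model rest on the same assumption, so their agreement would say little about loss that is not at random. The possible size is 1 to 3 min on a 9.9 min target, given 20 % loss and a departure of 5 to 15 min confined to one arm. It shrinks as the arms become alike, and vanishes with equal loss and equal departure.

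This rests on inference from standard properties of the methods, since the article never names missing at random, and on a simulation simpler than the trial's daily-measures model.

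Three stronger readings are not supported. The primary analysis is not shown to be biased: no passage says that children who leave are less active or that loss differs by arm. Missing data cannot be called the main threat to the result, because nothing in the document ranks the threats. And no analysis, delta-adjusted or otherwise, can test missing at random from the observed data; it can only show how large a departure would change the conclusion.

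The matter concerns a supporting analysis. It is worth correcting because this is the only check named for the planned loss.

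**What to change.** Keep the planned multiple imputation, with auxiliary variables if wished. Add a delta-adjusted (pattern-mixture) imputation that respects clustering by service. Shift the imputed follow-up MVPA over a range fixed in advance, separately by arm so that one-arm and unequal departures are covered, and report the tipping point at which the conclusion on the primary outcome changes. A range such as 0 to -15 min would cover the scenarios above, but it has no source in the protocol and needs a stated rationale.

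Reword the Abstract to say that the analysis explores sensitivity to departures from the missing-data assumption, and name that assumption as missing at random in the Analysis section.

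The cost is a few extra analysis runs and some wording; design, sample size and data collection do not change. The one real drawback is that the range of shifts must be chosen by judgement, which is why it should be set before follow-up data are seen.
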